### **Analysis of Safety Variables**

#### **Adverse Reactions**

Adverse reactions are defined as any unfavorable symptoms, signs, or diseases that occur in study participants after administration of the investigational product. Present the number of patients, incidence rate, frequency, and 95% confidence interval for all adverse reactions, adverse drug reactions (ADR), serious adverse reactions (SAE), and serious adverse drug reactions (SADR) for each intervention group. Differences between groups will be tested using the Chi-square test or Fisher's exact test. Code all adverse reactions using the MedDRA (Medical Dictionary for Regulatory Activities) by System Organ Class (SOC) and Preferred Term (PT), and present the frequency, proportion, and number of events for each group.

#### **Laboratory Tests, Vital Signs**

Present descriptive statistics for pre- and post-intervention values and changes in vital signs and quantitative laboratory test results for each group. Compare changes between groups using the independent two-sample t-test or Wilcoxon rank-sum test, and changes within each group using the paired t-test or Wilcoxon signed-rank test. Additionally, present contingency tables for dichotomous laboratory test results and ECG results showing changes from pre- to post-intervention categorized as normal (including clinically insignificant abnormal) or clinically significant abnormal. Test changes within each group using McNemar's test (or McNemar's Exact test).

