|                                                    | 
 
● Liver or kidney disease history or lab results exceeding 3 times the upper normal limit for AST, ALT, BUN, Creatinine.
 
● Women who are pregnant, may become pregnant, or are breastfeeding
 
● Participation in another study within the last 30 days
 
● Clinically significant psychiatric symptoms or medical conditions as judged by the investigator
 
                                                                                                                                                                                                                                                                                                                                                                                                          |       |                                     |
| Target Number of Participants               | This pilot study aims to recruit 100 participants, with 50 in the Kyungok-go treatment group and 50 in the placebo group.                                                                                                                                                                                                                                                                                                                                                                                                                                                                                                                                                                                                                                                                                                                     |       |                                     |

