### **2) Exclusion criteria**

- Individuals with a history or current condition of diseases that can cause fatigue (e.g., cancer, sleep disorders, chronic hepatitis, liver cirrhosis, chronic renal failure, tuberculosis, asthma, multiple sclerosis).
- Individuals with conditions that can affect drug absorption or metabolism (e.g., dysphagia, clinically significant gastrointestinal disorders, galactose intolerance, Lapp lactase deficiency, glucose-galactose malabsorption).
- Uncontrolled diabetic patients.
- Individuals with a history of allergies to the investigational medicinal product (herbal medicine).
- Individuals with a history of liver or kidney diseases, or blood tests showing AST, ALT, BUN,

or creatinine levels exceeding three times the upper limit of normal.

- Pregnant or breastfeeding women, or those with the potential to become pregnant.
- Individuals who have participated in another clinical trial within 30 days prior to the study.
- Individuals who have taken herbal or herbal medicine (containing the same ingredients as the investigational medicinal product) within two weeks prior to the study.
- Individuals whom the researcher deems unable to participate in the study due to clinically significant psychiatric symptoms, medical conditions, or laboratory findings.

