#### **11.4.2.9 Electrocardiogram examination**

Evaluate for severe heart diseases such as acute myocardial infarction and ventricular fibrillation.

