#### **14.4 Analysis of safety variables**

##### **14.4.1 Adverse events**

Adverse events (AEs) are defined as any unfavorable symptoms, signs, or diseases occurring in subjects administered the investigational medicinal product. The number of subjects experiencing all AEs, adverse drug reactions (ADRs), serious adverse events (SAEs), and serious adverse drug reactions (SADRs), along with their incidence rates and 95% confidence intervals, will be presented for each group. Differences between groups will be tested using the Chi-square test or Fisher's exact test. All AEs will be coded using the Medical Dictionary for Regulatory Activities (MedDRA) and presented by system organ class (SOC) and preferred term (PT).

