##### **14.4.2 Laboratory tests, vital signs**

Vital signs and quantitative laboratory test results, including heart rate variability, will be presented as descriptive statistics before and after administration for each herbal preparation group. Changes will be compared between groups using the independent two-sample t-test or Wilcoxon rank-sum test. Within-group changes will be tested using the paired t-test or Wilcoxon signed-rank test. Additionally, laboratory test results before and after administration will be categorized as normal (including clinically insignificant abnormal) or clinically significant abnormal changes. Changes within groups will be tested using McNemar's test (or McNemar's exact test).

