## 1 6. Methods, criteria, and interpretation for safety evaluation including adverse reactions

### 16.1 Evaluation methods

Adverse Event (AE) refers to any harmful and unintended sign (including abnormal laboratory results), symptom, or disease that occurs in a study participant who has been administered the herbal preparation, regardless of a causal relationship with the herbal preparation.

Adverse Drug Reaction (ADR) refers to any harmful and unintended reaction at any dose of the herbal preparation, where a causal relationship with the herbal preparation cannot be ruled out. In this study, all adverse events except those assessed as "unrelated" will be classified as ADRs.

The Case Report Form will document the symptoms and signs of adverse reactions, their duration (start and end dates), severity, causal relationship with the herbal preparation, actions taken regarding the adverse reaction, and outcomes comprehensively.

The safety evaluation will include:

- Adverse events, vital signs, laboratory tests, heart rate variability tests

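### Laboratory results (and, in the Summary, ECG) classed as clinically significant abnormal are tested only within each arm by McNemar's test, without the placebo comparison used for the other safety data

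*Protocol*

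**What the plan says.** The Summary, under Laboratory Tests, Vital Signs, asks for pre/post tables of dichotomous laboratory results and ECG in two classes: normal (which takes in abnormal but clinically unimportant results) and clinically significantly abnormal. The test is: "Test changes within each group using McNemar's test (or McNemar's Exact test". Section 14.4.2 repeats the rule for laboratory results, without naming ECG: "Changes within groups will be tested using McNemar's test (or McNemar's exact test". Neither place names a between-arm test for these classes.

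Other safety data are compared with placebo. For quantitative results the Summary says: "Compare changes between groups using the independent two-sample t-test or Wilcoxon rank-sum test". For adverse events section 14.4.1 says: "Differences between groups will be tested using the Chi-square test or Fisher's exact test". Section 16.1 defines an adverse event as "any harmful and unintended sign (including abnormal laboratory results), symptom, or disease", so abnormal laboratory results can enter that comparison.

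On entry, the Summary excludes people with "lab results exceeding 3 times the upper normal limit for AST, ALT, BUN, Creatinine". The exclusion criteria in section 7 add people whom the researcher considers unable to take part because of "clinically significant psychiatric symptoms, medical conditions, or laboratory findings". No ECG exclusion is listed; section 11.4.2.9 says only: "Evaluate for severe heart diseases such as acute myocardial infarction and ventricular fibrillation".

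**The concern.** In a randomised placebo-controlled trial, the safety question is whether more people develop a clinically significant abnormality on Kyungok-go than on placebo. McNemar's test asks something else: within one arm, are normal-to-abnormal and abnormal-to-normal shifts equally likely? If screening has removed most abnormal results, few can shift back. New abnormalities that arise for any reason then push the test towards rejection, in the placebo arm as much as in the active arm.

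Two misreadings follow. A result that is significant in one arm and not in the other can arise by chance and be taken as a drug signal. And when such events are rare, the test hardly ever rejects, so a non-significant p-value can be taken as reassurance that it does not give. This matters because section 27 lists liver dysfunction as a potential risk, and AST and ALT are among the four analytes repeated at Visit 4 (section 11.4.1.4).

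**Working it through.** The protocol gives no error rate, power or expected frequency for this analysis, so there is no figure to reproduce.

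**Inputs from the protocol.** 50 per arm with 1:1 allocation (sections 7 and 11.3); two-sided 5% level (section 14.1); exact or asymptotic McNemar (Summary and section 14.4.2).

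**Assumptions, not in the protocol.** No drug effect; all 50 per arm have Visit 4 data; the same background rate p of new clinically significant abnormality in both arms; and, at first, no abnormal result at baseline.

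**Step 1: rejection threshold.** Let b be the number of new abnormalities, with no reverse shifts.
- Exact two-sided p-value = 2 × 0.5^b. For b = 5 it is 0.0625; for b = 6 it is 0.031. The exact test needs 6 new cases.
- Uncorrected chi-square = b on 1 degree of freedom. For b = 3 the p-value is 0.083; for b = 4 it is 0.046. This version needs 4.

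**Step 2: chance of rejecting in one arm with no drug effect.** Exact: P(Bin(50, p) ≥ 6). Uncorrected: P(Bin(50, p) ≥ 4). The last column is Fisher's exact test between the arms, by full enumeration of 50 v 50.

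| Background rate p | Exact McNemar | Uncorrected McNemar | Fisher between arms |
|---|---|---|---|
| 2% | 0.05% | 1.8% | 0.04% |
| 5% | 3.8% | 24.0% | 0.7% |
| 8% | 20.8% | 57.5% | 1.5% |
| 10% | 38.4% | 75.0% | 1.8% |
| 15% | 78.1% | 95.4% | 2.4% |

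**Step 3: one arm significant, the other not.** At p = 10%, the exact test is significant for Kyungok-go only with probability 0.384 × (1 − 0.384) = 0.237, with no drug effect.

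**Step 4: allow abnormal results at baseline.** Let q be the baseline prevalence, with baseline and Visit 4 status independent. The probability of a new abnormality is (1 − q)p and of a resolution q(1 − p). At p = 10%, the exact test rejects as follows:

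| Baseline prevalence q | Exact McNemar |
|---|---|
| 0% | 38.4% |
| 2% | 19.8% |
| 5% | 6.9% |
| 10% | 2.1% |

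At q = 10% both shift probabilities are 0.9 × 0.1 = 0.09, so the null is true. The rejection rate moves from 38.4% to 2.1% with no change in treatment effect.

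**Step 5: an example.** With 6/50 new cases on Kyungok-go and 5/50 on placebo, exact McNemar gives p = 0.031 and p = 0.063. Fisher between the arms gives p = 1.00. The risk difference is 0.12 − 0.10 = 0.02, with standard error √(0.12 × 0.88/50 + 0.10 × 0.90/50) = 0.0625. The approximate 95% interval is 0.02 ± 1.96 × 0.0625, or −10 to +14 percentage points.

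**The case against.** Several stronger readings are tempting, and the protocol does not support them.

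- *The placebo arm goes unused for safety.* It does not. Quantitative laboratory changes are compared with placebo. Adverse events, which include harmful abnormal laboratory results, are compared by Chi-square or Fisher, and section 11.4.2.26 puts clinically significant laboratory changes under adverse event monitoring. Placebo also has its own shift table and McNemar test.
- *The McNemar null is false by design.* The numeric exclusion covers four analytes and only values above 3 times the upper limit. Values between 1 and 3 times may enter and could be judged clinically significant. Other removal rests on investigator judgement. For ECG no exclusion is listed, so the screening argument is not established there.
- *The test over-rejects.* The exact version does so only above a background rate of about 5%, and only with few abnormal results at baseline. The abnormal class is narrow, so low rates are plausible.
- *No between-group rule for categorical data exists.* Section 14.1 has one, by Chi-square or Fisher. It follows the efficacy ANCOVA rule, however, and section 14.4.2 sets its own test, so its reach is unclear.

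These points limit the size of the problem. They do not remove it. The stated adverse-event test covers totals (all events, drug reactions, serious events and serious reactions), while counts by organ class and term are only presented. A shift in ALT or ECG therefore has no explicit between-arm comparison of its own. Tests of mean or rank change do not count how many participants became clinically abnormal, and they do not cover ECG.

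**Conclusion.** The point stands as a minor, secondary safety matter. For these classes, the only test named in the two laboratory and vital-sign passages is a within-arm test that cannot separate a drug effect from background change. Its p-value depends on the background rate and on how many abnormal results pass screening.

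The size is conditional. With 50 per arm, no baseline abnormalities and no drug effect, the exact test is nearly silent at a 2% rate (0.05%), below nominal at 5% (3.8%) and well above it at 8% and 10% (20.8% and 38.4%). The uncorrected version, which the wording also allows, is already at 24.0% at a 5% rate. If baseline prevalence is 10%, the exact figure at a 10% rate is about 2%. The documents give neither rate, so none of these is a prediction. The primary endpoint is not affected.

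**What to change.** In section 14.4.2 and in the Summary:
- keep the pre/post shift tables, as description only;
- drop the McNemar p-value as the inferential result;
- for each repeated analyte and for ECG, report per arm the number and proportion with a new clinically significant abnormality at Visit 4 among those without one at baseline;
- give the between-arm risk difference with its 95% confidence interval, and Fisher's exact test if a p-value is wanted;
- name ECG in both places, since section 14.4.2 now omits it.

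The cost is a sentence or two in each place. The data are already collected, and no visit or test is added. The downside is low power: with 50 per arm, Fisher's test has about 19% power for 2% versus 10%. A non-significant p-value will not show safety either, so the interval has to carry the message.

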## List of Abbreviations

|           |                                                   |
|-----------|---------------------------------------------------|
| ADR       | Adverse Drug Reaction                             |
| A.E.      | Adverse Event                                     |
| ALT       | Alanine Transaminase                              |
| AST       | Aspartate aminotransferase                        |
| BDI       | Becks' depression inventory                       |
| BMI       | Body Mass Index                                   |
| BUN       | Blood Urea Nitrogen                               |
| C.K.      | Creatine Kinase                                   |
| CFS       | Chronic Fatigue Syndrome                          |
| ChF S     | Chalder Fatigue Scale                             |
| C OVID-19 | Coronavirus disease 2019                          |
| CRP       | C-Reactive Protein                                |
| DB        | Digit span backward                               |
| D F       | D igit span forward                               |
| EPO       | Erythropoietin                                    |
| EQ-5D     | EuroQol five dimensions questionnaire             |
| FAS       | Full Analysis Set                                 |
| FSS       | F atigue severity scale                           |
| F /U      | F ollow-up                                        |
| GCP       | Good Clinical Practice                            |
| Hb        | Hemoglobin                                        |
| HBV       | Hepatitis B Virus                                 |
| Hct       | Hematocrit                                        |
| HCV       | Hepatitis C Virus                                 |
| HIV       | Human Immunodeficiency Virus                      |
| ICH       | International Conference on Harmonization         |
| IRB       | Institutional Review Board                        |
| ITT       | Intent To Treat                                   |
| K-MOCA    | Korean-Montreal cognitive assessment              |
| K-WAIS-IV | Korean Wechsler Adult Intelligence Scale-IV       |
| LDH       | Lactate Dehydrogenase                             |
| LOCF      | Last Observation Carried Forward                  |
| MedDRA    | Medical Dictionary for Regulatory Activities      |
| PSQI-K    | English version of Pittsburgh Sleep Quality Index |
| R.B.C.    | Red Blood Cell                                    |
| SADR      | Serious Adverse Drug Reaction                     |
| S.A.E.    | Serious adverse event                             |
| SPPB      | S hort physical performance battery               |
| TSH       | Thyroid Stimulating Hormone                       |
| U.N.L.    | Upper Normal Limit                                |
| WBC       | White Blood Cell                                  |

## Schedule Summary

| Visit                                                                      | 0       | One  | 2      | 3      | 4       | UV * |
|----------------------------------------------------------------------------|---------|------|--------|--------|---------|------|
| Week (day)                                                                 | -1 (-7) | 1(0) | 4 (28) | 8 (56) | 12 (84) | -    |
| Visit window (day)                                                         | -       | +2   | ±2     | ±2     | ±2      | -    |
| Written Consent                                                            | ●       |      |        |        |         |      |
| Demographic Survey                                                         | ●       |      |        |        |         |      |
| Participation in Other Clinical Trials                                     | ●       |      |        |        |         |      |
| Physical Exam                                                              | ●       |      |        |        |         |      |
| Medical History                                                            | ●       | ●    |        |        |         |      |
| COVID-19 Diagnosis                                                         | ●       |      |        |        |         |      |
| Concomitant Medication/Treatment                                           | ●       |      |        |        |         |      |
| Vital Signs                                                                | ●       | ●    | ●      | ●      | ●       | ●    |
| Electrocardiogram                                                          | ●       |      |        |        | ●       | ●    |
| Laboratory Test                                                            | ●       |      |        |        | ●       | ●    |
| Immune, Metabolite Test (Blood Collection)                                 | ●       |      |        |        | ●       | ●    |
| Pregnancy Status Evaluation **                                             | ●       |      |        |        |         |      |
| Fatigue Symptom Evaluation ***                                             | ●       |      |        |        |         |      |
| FSS (Fatigue Severity Scale)                                               | ●       |      | ●      | ●      | ●       | ●    |
| Inclusion and Exclusion Criteria Evaluation                                | ●       |      |        |        |         |      |
| Random Assignment                                                          |         | ●    |        |        |         |      |
| Prescription and Delivery of Assigned Intervention (Kyungok-go or placebo) |         | ●    | ●      | ●      |         |      |
| Compliance check                                                           |         |      | ●      | ●      | ●       | ●    |
| Combined Medication Evaluation                                             |         |      | ●      | ●      | ●       | ●    |
| 0-100 VAS (Visual Analogue Scale) of Fatigue                               |         | ●    | ●      | ●      | ●       | ●    |
| CHFS (Chalder Fatigue Scale)                                               |         | ●    | ●      | ●      | ●       | ●    |
| EQ-5D-5L                                                                   |         | ●    |        |        | ●       | ●    |
| PSQI- K (Korean version of Pittsburgh Sleep Quality Index)                 |         | ●    |        |        | ●       | ●    |
| K- MOCA (Korean-Montreal Cognitive Assessment)                             |         | ●    |        |        | ●       | ●    |
| BDI (Becks' Depression Inventory)                                          |         | ●    |        |        | ●       | ●    |
| Test for Memorizing Numbers Straight/Reverse                               |         | ●    |        |        | ●       | ●    |
| Computerization Neurocognitive Function Test Score                         |         | ●    |        |        | ●       | ●    |
| SPPB (Short Physical Performance Battery)                                  |         | ●    |        |        | ●       | ●    |
| Adverse Reaction Inspection                                                |         |      | ●      | ●      | ●       | ●    |

● Conducted at that visit ; \*UV: Unscheduled visit (visiting on a day other than the original visit schedule due to adverse reactions, etc.); \* \* Only for women of childbearing age ; \*\*\* To evaluate the selection criteria, we investigated whether fatigue occurred after becoming sick with COVID-19.

### 1. Title and Phase of the Clinical Trial

Clinical Trial to Evaluate the Efficacy of Kyungok-go for Fatigue in Patients with Long COVID:

A Double-Blind, Randomized, Multi-Center, Preliminary, Investigator-Initiated Trial

Phase : Not applicable

## 5. Background and Purpose of the Clinical Trial

### 1) Research background

#### Status of Post-COVID-19 Sequelae

Due to the global pandemic of coronavirus disease-19 (COVID-19), medical and research efforts have been concentrated on developing vaccines to prevent infection, halting the spread of the virus, and treating acute infections. However, in addition to the life-threatening acute infections, post-COVID-19 sequelae are also being widely reported. A research team from the University of Michigan conducted telephone interviews to investigate the presence of sequelae in 1,250 severe COVID-19 patients who were hospitalized in 38 hospitals in Michigan, USA, from spring to summer 2020. Among the 488 respondents, about 39% reported that they could not perform normal activities even two months after discharge, and 12% stated that it was difficult to manage daily activities on their own as they did before contract COVID-19. Additionally, 23% reported experiencing shortness of breath when climbing stairs, and one-third mentioned persistent acute symptoms such as loss of taste or smell. Moreover, 40% of the respondents were unable to return to their previous jobs due to health issues, with some becoming unemployed, and 26% of those who returned to work had to reduce their working hours due to health problems [1]. These findings highlight the severe impact of post-COVID-19 sequelae, comparable to the acute symptoms of the disease.

A recent study on the prevalence of post-COVID-19 sequelae reported that fatigue is the most common symptom, affecting 28.4% of hospitalized patients and 34.5% of outpatients among 735,006 COVID-19 patients [2]. Researchers at Trinity College Dublin conducted a follow-up study on 128 COVID-19 patients who were either hospitalized or received outpatient treatment at St. James's Hospital in Dublin. Over half of these patients (52.3%) reported experiencing fatigue for at least six weeks after being diagnosed with COVID-19, with some severe cases

experiencing fatigue for up to 10 weeks. In contrast, 54 respondents (42.2%) reported no post-COVID-19 sequelae. Interestingly, the study found no correlation between the severity of COVID-19 and the level of fatigue, indicating that more than half of the COVID-19 survivors experienced fatigue regardless of the severity of their initial symptoms [3]. The symptoms experienced after recovering from COVID-19 are highly variable, and their mechanisms are not yet clearly understood. However, chronic fatigue syndrome (CFS) has been observed in patients who have suffered from various viral infections. Approximately 27% of survivors of the 2003 SARS outbreak were reported to exhibit CFS symptoms years after their diagnosis [4]. Thus, it is reasonable to consider these symptoms as part of the broader category of post-viral fatigue syndrome.

This situation applies equally to South Korea. On September 29, the Central Disease Control Headquarters announced in a regular briefing that more than 90% of COVID-19 survivors experienced sequelae such as fatigue and decreased concentration. Deputy Director Kwon Jun-wook of the Central Disease Control Headquarters reported that in a survey conducted by Kyungpook National University Hospital involving 5,762 participants, 965 respondents provided answers regarding post-COVID-19 sequelae, with 91.1% (879 respondents) indicating that they experienced at least one sequela. The most common sequelae reported in South Korea include fatigue (26.2%) and decreased concentration (24.6%), as well as psychological and mental sequelae, and loss of smell and taste [5]. This indicates a growing need for treatment strategies for post-COVID-19 sequelae as part of the overall management of the disease.

